# Effect of preoperative CT angiography examination on the clinical outcome of patients with BMI ≥ 25.0 kg/m^2^ undergoing laparoscopic gastrectomy: study protocol for a multicentre randomized controlled trial

**DOI:** 10.1186/s13063-021-05887-1

**Published:** 2021-12-11

**Keywords:** Gastric cancer, CTA, Laparoscopic gastrectomy, Clinical outcomes, Study protocol, Randomized controlled trial

## Abstract

**Background:**

Gastric cancer, which is the fifth most common malignancy and the third most common cause of cancer-related death, is particularly predominant in East Asian countries, such as China, Japan and Korea. It is a serious global health issue that causes a heavy financial burden for the government and family. To our knowledge, there are few reports of multicentre randomized controlled trials on the utilization of CT angiography (CTA) for patients who are histologically diagnosed with gastric cancer before surgery. Therefore, we planned this RCT to verify whether the utilization of CTA can change the short- and long-term clinical outcomes.

**Method:**

The GISSG 20–01 study is a multicentre, prospective, open-label clinical study that emphasises the application of CTA for patients who will undergo laparoscopic gastrectomy to prove its clinical findings. A total of 382 patients who meet the inclusion criteria will be recruited for the study and randomly divided into two groups in a 1:1 ratio: the CTA group (*n* = 191) and the non-CTA group (*n* = 191). Both groups will undergo upper abdomen enhanced CT, and the CTA group will also receive CT angiography. The primary endpoint of this trial is the volume of blood loss. The second primary endpoints are the number of retrieved lymph nodes, postoperative recovery course, hospitalization costs, length of hospitalization days, postoperative complications, 3-year OS and 3-year DFS.

**Discussion:**

It is anticipated that the results of this trial will provide high-level evidence and have clinical value for the application of CTA in laparoscopic gastrectomy.

**Trial registration:**

ClinicalTrials.gov, NCT04636099. Registered November 19, 2020

**Supplementary Information:**

The online version contains supplementary material available at 10.1186/s13063-021-05887-1.

## Introduction

### Background and rationale

Since the first report of laparoscopic assisted-distal gastrectomy by Kitano in 1994 [1], it has gained great acceptance by surgeons and patients for treating surgically resectable gastric malignancy without bulky lymph nodes or lesions. It is a minimally invasive surgical procedure and has an enhanced recovery course and comparable oncological efficiency compared with that of open surgery, which has been demonstrated by some large-scale multicentre randomized controlled trials [2–7]. Although gastric cancer multimodal treatment has achieved excellent results, such as chemotherapy and immunity therapy, which have significant oncological advantages for treating advanced gastric malignant tumours, surgery is still the mainstream curative treatment for patients diagnosed with gastric cancer.

Radical lymphadenectomy associated with gastrectomy is an essential principle of the treatment of gastric cancer [8, 9]. The distribution of the lymph nodes along the vessels needs to be considered. The number of harvested positive lymph nodes is of great importance for predicting the long-term survival of patients, but even among skilled surgeons, lymphadenectomy is a challenging and tricky task, not only due to its technical difficulty in separating the lymph nodes from their surrounding tissues but also due to in some circumstances the difficulty of distinguishing bulky lymph nodes from the main perigastric arteries, such as the right gastric artery, common hepatic artery and spleen artery.

Because of the complexity and individual variations of the perigastric vessels, apart from the necessity of gaining familiarity with normal anatomical perigastric vessels before surgery, preoperative acquaintance with any aberrant anatomy of the vessels can help avoid intraoperative damage to the vessels, such as the left gastric artery and common hepatic artery, which can reduce intraoperative blood loss, protect the liver from dysfunction and achieve a fast postoperative recovery [10].

Although digital subtraction angiography (DSA) is regarded as the gold standard to detect the anatomical position and variations of the vessels [11], because of its invasive operation and relatively high expense, it has been replaced by CT angiography (CTA) in the field of gastrectomy for the purpose of leaning the variations of the perigastric vessels before surgery, and it can provide a three-dimensional image of the perigastric vessels [12, 13].

Some studies have already declared the usefulness of the application of CT angiography before surgery. Iino et al. demonstrated that preoperative acquisition of perigastric vessel information might contribute to the safe dissection of lymph nodes during laparoscopic gastrectomy [12]. According to the study of Mu et al. [14], the surgeon can have a good acquaintance of celiac artery on its origin, course and variation and vascular calcifications for the patients that underwent gastrectomy with the help of 64-MSCTA, and it is also recommended that CTA should be a preoperative conventional procedure in gastric cancer patients.

Based on a retrospective propensity score matching study [15], we proposed a novel classification of the perigastric vessels according to the processing of CTA images, which indicates that utilizing CTA can further improve short-term clinical recovery course including more harvest of lymph nodes and less estimated blood loss and operation time, compared with patients who received abdominal enhanced CT without CTA, especially for patients whose BMI ≥ 25 kg/m^2^. To the best of our knowledge, few multicentre randomized controlled prospective studies have focused on the application of CTA for patients who are diagnosed with gastric cancer before undergoing laparoscopic gastrectomy.

For further research, we planned this multicentre controlled trial, which is named after GISSG 20–01, to verify whether the use of CTA can improve the short- and long-term clinical outcomes of patients who undergo laparoscopic or robotic gastrectomy.

## Methods/design

### Objective

The aim of the GISSG20–01 study is to explore the short-term clinical recovery course and the long-term oncological effects of preoperative CTA for patients who undergo laparoscopic or robotic gastric cancer radical surgery.

### Trial design

The GISSG20–01 study is a multicentre, prospective, open-label clinical study in which patients who meet the inclusion criteria will be randomly assigned to an experimental group (CTA group) and a control group (non-CTA group) in a 1:1 ratio. In addition to the standard examinations in both groups, the patients in the CTA group will receive upper abdomen enhanced CT and CT angiography while the non-CTA group will receive upper abdomen enhanced CT only.

### Participant selection

Patients who are diagnosed with gastric cancer and plan to undergo laparoscopic or robotic gastrectomy will be enrolled from the 14 centres listed in Table 1. The launching conference was held online and was used to inform the participating staff about the details of the GISSG 20–01 trial. To obtain enough enrolled patients, all gastrointestinal surgeons in the participating centres were informed that the clinical trial was recruiting, and hospitalized patients were given the details about the trial for the purpose of enrolment. There are usually four ways to recruit patients: inpatients of gastrointestinal surgery, outpatients of gastrointestinal surgery, displaying poster at outpatient clinic or releasing recruitment information on the Internet. The enrolment of the first patient was started in November 2020, while it is anticipated that the deadline for the recruitment of the patients will be in November 2021. In the end, 382 patients who meet the inclusion criteria will be included in this trial. The study protocol and informed consent form were approved by the ethics review board of all research hospitals before the enrolment of any patients. Well-trained research doctors are responsible for introducing the main contents of the study to the patients and obtaining informed consent from patients who voluntarily participate in the trial in each centre. The flowchart that demonstrates the process of enrolment of the patients is shown in Fig. 1. The study protocol was revised to version 1.3 in December 2020. Any major modifications to the study protocol that may have a significant influence on the execution of the trial, including changes in the inclusion or exclusion criteria, number of samples or the study design, will require a formal amendment to the protocol. Such major modifications will be agreed up on by the GISSG (Gastrointestinal Surgery Study Group) and approved by the ethics review board. Protocol modifications are transmitted through the research meeting, and the electronic manual is distributed to the sub-centre researchers. An integral checklist of items in accordance with SPIRIT (Standardized Protocol Items: Recommendations for Intervention Trials) (2013 version) was supplied in additional file 1.

**Table 1 Tab1:** The 14 participating centres

Number	Centre	Department	Investigator
01	The Affiliated Hospital of Qingdao University	Gastrointestinal Surgery	[name]

**Fig. 1 Fig1:**
[figure not shown]
Study flowchart. CTA, CT angiography

### Inclusion and exclusion criteria

The inclusion criteria are as follows: (1) patients with a pathological diagnosis of gastric adenocarcinoma by gastroscopy, (2) patients aged between 18 and 75 years old, (3) patients with a body mass index (BMI) not less than 25.0 kg/m^2^, (4) tumour clinical stage evaluated by CT imaging (T1~T4a, N0~3, M0), (5) patients with an Eastern Cooperative Oncology Group (ECOG) score 0–1 points, (6) the surgical approach is laparoscopic or robotic surgery, and (7) patients who are willing to participate in the study and sign the informed consent form.

The exclusion criteria are as follows: (1) patients whose tumour clinical stage conformed to T4b or M1 and whose tumour was found to be unresectable during the operation; (2) patients who suffered from a history of other malignant tumours or tumours of low malignant potential (such as giant cell tumours of the bone, pseudomyxadenoma of the appendix, invasive fibroma); (3) patients who have other serious systemic diseases and could not tolerate the trauma of surgery; (4) patients with non-adenocarcinoma-type malignant tumours verified by pathology after surgery; (5) patients with residual gastric cancer; (6) patients who are allergic to iodine contrast agents; (7) patients who received neoadjuvant therapy before surgery; (8) pregnant or lactating patients; and (9) patients who are participating in other clinical trials.

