### Randomization

In this trial, eligible patients will be randomly assigned to either the CTA group or the non-CTA group in a 1:1 ratio. A central dynamic, stratified strategy was adopted for the aim of randomization. The sequence of randomization was generated by a certain doctor who was independent of this trial using the method of Pocock-Simon minimization by SAS 9.3 (SAS Institute Inc., Cary, NC, USA) and stratified by participating site (14 hospitals) and surgical approach (laparoscopic or robotic). The above information provided by the participating centres was submitted to the data centre at the Department of Gastrointestinal Surgery, Affiliated Hospital of Qingdao University, China, where central randomization was executed. Consequently, the allocation information will then be sent to each participating site. The allocation procedure was not blinded to the investigators or patients but was masked for data collection and analysis.

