A preoperative mandatory abdominal enhanced CT scan will be performed in both the experimental group and the control group to evaluate the clinical stage of the tumour. Moreover, compared with the non-CTA group, the patients in the CTA group will be asked to undergo the CTA examination once they are randomly assigned to the experimental group. To improve adherence to the intervention protocols, the patients will be fully informed of the potential short-term clinical recovery course and long-term oncological effects. Regular research meetings are held to provide relevant study guidance for researchers. For the researchers, there are mainly three ways to enhance adherence to intervention protocols including researcher training, regular researcher meetings and regular visits to the sub-centres. Abdominal enhanced CT will be performed using a 64-detector row CT scanner in this study, while the type of CT equipment is according to what is available in each participating centre. The procedure of the abdominal enhanced CT was set to ensure the same standard for the reconstruction of the perigastric arteries across centres. Fasting no less than 8 h before the examination is required, and an injection of 10 mg anisodamine 10 min before the examination is necessary for the purpose of reducing gastric distention and motility. Nonionic iodinated contrast material will be used as the contrast agent, injected at a speed of 4.0 ml/s by an automatic injector, and its volume is based on the weight of the patient; for example, for patients weighing 60 kg or less, the lower limit is 120 ml, and for patients weighing more than 75 kg, the upper limit is 150 ml.

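### Two exclusion criteria can only be met during or after surgery, so applying them as written removes randomised patients

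*Protocol article*

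**What the plan says.** In the Protocol article, under Inclusion and exclusion criteria, exclusion criterion 1 covers "patients whose tumour clinical stage conformed to T4b or M1 and whose tumour was found to be unresectable during the operation", and criterion 4 covers "patients with non-adenocarcinoma-type malignant tumours verified by pathology after surgery".

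Under Interventions and CTA protocol, assignment comes before the extra imaging: "the patients in the CTA group will be asked to undergo the CTA examination once they are randomly assigned to the experimental group". Under Randomization, the article states that "The allocation procedure was not blinded to the investigators or patients but was masked for data collection and analysis".

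The section on Outcomes makes blood loss during the operation the primary endpoint. Under Data collection and analysis, OS and DFS are counted from surgery. The article nowhere says that a randomised patient who later meets criterion 1 or 4 stays in the analysis in the allocated group.

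**The concern.** Randomisation protects a comparison only if the patients analysed are those randomised, or if the losses have nothing to do with allocation and outcome. An exclusion criterion that depends on an operative finding or a surgical specimen acts after allocation.

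Unresectability is the more serious of the two. It is a judgement made by a surgeon who knows the arm. In the CTA arm the team has also studied the arterial reconstructions. The judgement falls within the procedure whose blood loss is the primary endpoint. The exclusion may therefore be related both to allocation and to outcome. Survival is affected too, since patients whose tumour cannot be removed can be expected to do worse.

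The pathology criterion is milder. Histology is fixed before randomisation and imaging cannot change it, and inclusion criterion 1 already requires adenocarcinoma on gastroscopic pathology. It should remove few patients, and about equally from both arms, but those it removes were randomised.

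**Working it through.** **Timing.** The article gives the order: assignment, then CTA in the experimental group, then surgery, then specimen pathology. An intraoperative finding and a postoperative diagnosis both lie after assignment, so no reading of criteria 1 and 4 lets them be settled in full at entry.

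**Reach of criterion 1.** It joins stage T4b or M1 to unresectability with 'and'.
- If both conditions are needed, few patients are affected: inclusion criterion 4 already limits entry to CT stage T1–T4a, N0–3, M0.
- If either condition is enough, every patient found unresectable at operation is removed.

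The text does not settle which is meant. Both readings make an operative finding part of an eligibility rule.

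**The plan's own sample size.** Inputs from Sample size computation: 72.5 ± 66.4 ml and 93.5 ± 88.4 ml, one-sided α 0.05, power 80%, dropout about 10%.
- Difference: 93.5 − 72.5 = 21.0 ml.
- SD: √[(66.4² + 88.4²)/2] = √6111.76 = 78.18 ml.
- n per group: 2 × (1.645 + 0.842)² × 78.18² / 21² ≈ 171.4, so 172. The exact t calculation gives 173.
- Dropout: 173 × 1.1 = 190.3, so 191 per group and 382 in total.

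The planned 382 is reproduced, so 21 ml and SD 78.18 ml are fair yardsticks.

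**Effect on power.** Exclusions on top of 10% dropout leave 191 × 0.9 × (1 − e) per group:

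| Extra exclusion e | Power |
|---|---|
| 0 | 0.801 |
| 2% | 0.794 |
| 5% | 0.783 |
| 10% | 0.764 |

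Loss of power is minor. The issue is bias.

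**Effect on the estimate.** Let g be the between-arm difference in exclusion rate, and D the amount by which the excluded patients' blood loss differs from that of the rest. With no true effect, an arm that keeps these patients has mean μ + gD and an arm that drops them has mean μ. The spurious difference is therefore b ≈ g × D. With 172 per group, SE = 78.18 × √(2/172) = 8.43 ml. If b favours CTA, the one-sided type I error is 1 − Φ(1.645 − b/8.43). The article gives neither g nor D, so the values below are assumptions.

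| g | D (ml) | b (ml) | b / 21 | Type I error |
|---|---|---|---|---|
| 1 point | 50 | 0.5 | 2% | 0.056 |
| 2 points | 100 | 2.0 | 10% | 0.080 |
| 2 points | 200 | 4.0 | 19% | 0.121 |
| 5 points | 200 | 10.0 | 48% | 0.323 |

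Two points is about 4 of 191 patients. If g is zero, b is zero. If the sign of g or D reverses, the bias runs against CTA.

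**The case against.** **Analysis sets.** The strongest reply is that the article does not say such patients leave the analysis, and that analysis sets are commonly left to a statistical analysis plan or full protocol, neither of which is shown. This stands in part. A reader might infer that the randomised comparison is already lost, but that follows only if the criteria are applied as written. The point does not rest on a missing definition, however. Eligibility is fixed in this document, the plain meaning of an exclusion criterion is that the patient is out, and an analysis plan that kept these patients would conflict with it.

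**Staging CT.** A reader might also infer that staging, and hence eligibility, is settled after assignment, because "A preoperative mandatory abdominal enhanced CT scan will be performed in both the experimental group and the control group to evaluate the clinical stage". The documents do not support that. The sentence gives no time relative to assignment; only CTA is timed that way. The Randomization section says "eligible patients will be randomly assigned to either the CTA group or the non-CTA group in a 1:1 ratio", which implies that staging came first. The flowchart is not shown. This leaves a wording point, not a further exclusion after randomisation.

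**Mechanism.** One might suppose that operations abandoned after vascular injury and heavy bleeding would be counted as unresectable. Nothing in the article says so; the criterion concerns the tumour. A procedure stopped early could equally involve less bleeding, which would reverse the bias.

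**Reach.** The narrow reading of 'and' would leave criterion 1 with little effect after randomisation. That is a fair limit on the likely size, and also a reason to clear up the wording.

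**Conclusion.** The point holds: two stated exclusion criteria depend on facts that arise only after randomisation, and applying them removes randomised patients. Unresectability is the one that matters for bias, in blood loss and in OS and DFS. The pathology criterion is a lesser breach, unlikely to differ by arm.

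Neither the size nor the direction of any bias can be determined from the article. A moderate illustration, assuming a 2-point difference in exclusion and 100–200 ml difference in blood loss, gives 2–4 ml, or 10–19% of the 21 ml planning difference. A reader might prefer a harsher figure: with lognormal blood loss at the control mean and SD, dropping the top 2% from one arm alone lowers its mean by 8.1 ml, 39% of 21 ml. That requires every excluded patient to be among the heaviest bleeders (above about 351 ml, averaging about 490 ml) and all of them to be in one arm. Nothing in the documents supports this, so it should not be taken as the expected size.

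**What to change.** 1. Limit the eligibility criteria to facts known before randomisation, by removing the intraoperative condition from criterion 1 and the postoperative-pathology condition in criterion 4. This also removes the ambiguity of 'and'.
2. Keep such patients in the primary analysis in their allocated group, with blood loss counted for abandoned procedures. Everyone who would meet either condition has been operated on, so the endpoint can be measured.
3. Analyse OS and DFS by allocated group. If patients who are not operated on are to be included, count time from randomisation, because the present definitions start at surgery and give those patients no time origin.
4. Show the present exclusions only as a sensitivity analysis, with counts and reasons by arm.
5. As a minor clarification, state that the staging CT precedes randomisation.

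The cost is a formal amendment. Under Participant selection, a change to the eligibility criteria needs the study group's agreement and ethics approval, and here it must reach 14 centres while recruitment is under way. The analysis gains slight noise from a few atypical operations. The sample size need not change on this account.

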### Randomization

In this trial, eligible patients will be randomly assigned to either the CTA group or the non-CTA group in a 1:1 ratio. A central dynamic, stratified strategy was adopted for the aim of randomization. The sequence of randomization was generated by a certain doctor who was independent of this trial using the method of Pocock-Simon minimization by SAS 9.3 (SAS Institute Inc., Cary, NC, USA) and stratified by participating site (14 hospitals) and surgical approach (laparoscopic or robotic). The above information provided by the participating centres was submitted to the data centre at the Department of Gastrointestinal Surgery, Affiliated Hospital of Qingdao University, China, where central randomization was executed. Consequently, the allocation information will then be sent to each participating site. The allocation procedure was not blinded to the investigators or patients but was masked for data collection and analysis.

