### Outcomes

The primary endpoint of this trial is the volume of blood loss that occurs during the surgery. The second primary endpoints are as follows: (1) the harvested number of lymph nodes is defined as the dissection number of lymph nodes through the standard extent of lymph node dissection, which is conducted with the principal of lymph node dissection guided by the 2018 version of Japanese Gastric Cancer Treatment Guidelines; (2) postoperative recovery course, which refers to the items of time to first ambulation, flatus, liquid diet and so on; (3) hospitalization costs are defined as the total expenses during hospitalization brought on by treatment and care; (4) length of hospitalization days, which is defined as from the day of surgery to the day of discharge; and (5) the severity of postoperative complications, which include anastomotic leakage, pancreatic fistula, and pulmonary or abdominal infection, and are evaluated by the classification of Clavien–Dindo [16]. Complications were recorded when they were worse than grade II. Moreover, 3-year OS (overall survival) and 3-year DFS (disease-free survival) will also be followed up and recorded.

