### Data collection and analysis

An a priori designed and coincident case report form (CRF) will be used to record the information required by the study, such as baseline characteristics, laboratory data, perioperative clinical recovery course and long-term oncological outcomes, and a designated clinical investigator is responsible for the collection of data at each centre. Moreover, to keep track of changes to the data, any correction to the raw data requires signing the date and the investigator’s name. A monthly data check that includes data summarized by each centre, abnormal data and delayed data in progress tracking is required during the trial period.

Continuous variables will be presented as the mean ± standard deviation, while classification variables will be described as numbers (*N*) and percentages (%) to express the difference between two groups. To compare continuous variables for the two groups, Student’s *t* tests or Mann–Whitney *U* tests will be performed, and categorical variables will use the *χ*^2^ test or Fisher’s exact test. OS and DFS, defined as the time from surgery to death and the time from surgery to tumour recurrence or death from any cause, respectively, will be assessed by the Kaplan–Meier method with the log-rank test to analyse the differences in the survival curves. A Cox proportional hazards regression model with a 95% confidence interval will be used to perform univariate and multivariate analyses. Subgroup analyses will also be performed, with participants stratified by BMI (25.0 to 29.9 kg/m^2^, ≥ 30 kg/m^2^), to verify the effect of CTA on short-term and long-term clinical outcomes in overweight and obesity patients between CTA group and non-CTA group. For missing data, multiple imputation was used to obtain complete datasets. A *P* value less than 0.05 will be considered statistically significant. The 25th version of SPSS (SPSS Inc., Chicago, IL, USA) will be used to analyse the data.

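### Allocation is minimised on site and surgical approach, but the planned tests ignore both factors; if they are prognostic, standard errors are overstated and precision is forgone

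*Protocol article*

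**What the plan says.** The Randomization section of the protocol article describes central allocation, with patients "randomly assigned to either the CTA group or the non-CTA group in a 1:1 ratio", "using the method of Pocock-Simon minimization by SAS 9.3" and "stratified by participating site (14 hospitals) and surgical approach (laparoscopic or robotic".

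The Outcomes section states: "The primary endpoint of this trial is the volume of blood loss that occurs during the surgery". The Data collection and analysis section names the tests:

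- Continuous outcomes: "To compare continuous variables for the two groups, Student’s *t* tests or Mann–Whitney *U* tests will be performed".
- Categorical outcomes: "categorical variables will use the *χ*^2^ test or Fisher’s exact test".
- OS and DFS: these "will be assessed by the Kaplan–Meier method with the log-rank test to analyse the differences in the survival curves", with no strata mentioned.

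No comparison is adjusted or stratified for site or approach. The only multivariable model is a Cox regression, which cannot serve blood loss and whose covariates are not named. The only stratifying variable in the analysis is BMI, for subgroups. The Sample size computation section also uses a plain two-sample t test, one-sided.

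**The concern.** Minimisation makes the arms nearly alike in their mix of hospitals and approaches. Differences in blood loss between hospitals, or between laparoscopic and robotic surgery, then largely cancel out of the difference in means. An unadjusted two-sample test does not know this. Its standard error uses the total within-arm variance, including the part that the design has already removed.

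If site and approach predict blood loss, the reported standard error exceeds the true one, confidence intervals are too wide, and the true type I error falls below nominal. What is at stake is efficiency: the trial balances on two factors and then does not use the precision which that balance provides.

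**Working it through.** **Inputs from the Sample size computation section.** Mean blood loss is 72.5 (SD 66.4) ml with CTA and 93.5 (SD 88.4) ml without. The level is one-sided α = 0.05, power is 80% and dropout about 10%.

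**Reproducing the plan's figure.** The difference is 93.5 − 72.5 = 21.0 ml. The pooled SD is √[(66.4² + 88.4²)/2] = 78.18 ml.

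n per arm = 2(1.645 + 0.842)² × 78.18² / 21² = 171.4. Dividing by 0.9 gives 190.4, rounded up to 191 per arm, or 382 in total. The stated size therefore follows from an unadjusted one-sided t test of a 21 ml difference, with no margin in the calculation. About 172 per arm remain evaluable.

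**Effect of ignoring the factors.** Let R² be the share of within-arm variance that site and approach explain. The document gives no value, so R² is assumed to lie between 0 and 0.20.

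- SE used by the unadjusted test: 78.18 × √(2/172) = 8.43 ml.
- True SE under near-perfect balance: 8.43 × √(1 − R²).
- Overstatement of the SE: 1/√(1 − R²) − 1.
- True one-sided type I error: 1 − Φ(1.645/√(1 − R²)).
- Unadjusted power: Φ[(21 − 1.645 × 8.43)/true SE].
- Adjusted power: Φ[21/true SE − 1.645].

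| R² | True SE (ml) | SE overstated | True type I error | Power, unadjusted | Power, adjusted |
|---|---|---|---|---|---|
| 0 | 8.43 | 0% | 0.050 | 80.1% | 80.1% |
| 0.05 | 8.22 | 2.6% | 0.046 | 80.7% | 81.9% |
| 0.10 | 8.00 | 5.4% | 0.042 | 81.4% | 83.7% |
| 0.20 | 7.54 | 11.8% | 0.033 | 82.8% | 87.3% |

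At R² = 0.20 the half-width of a 95% interval would be 1.96 × 8.43 = 16.5 ml unadjusted, against 1.96 × 7.54 = 14.8 ml.

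**Check by simulation.** These formulas assume near-perfect balance. Minimisation was therefore simulated with 14 sites, two approaches and 344 patients (3,000 runs per setting), comparing a t test with a linear model containing site and approach.

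- Site intraclass correlation 0.10 and approach share 0.05 (R² about 0.15): the t test reported a mean SE of 8.40 ml against an actual 7.74 ml, with type I error 0.037 and power 81.0%. The adjusted model had a mean SE of 7.78 ml, type I error 0.047 and power 84.5%. The formulas at R² = 0.15 give a true SE of 7.77 ml and type I error of 0.037.
- No prognostic effect: power was 80.6% unadjusted and 80.4% adjusted, so fitting the extra terms costs almost nothing.

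**The case against.** The strongest defence is that a journal article condenses the plan and that covariates are commonly left to the SAP. The list of tests is generic and does not exclude adjustment. This does not dispose of the point. The article names specific unadjusted tests and sizes the trial on the same t test, so the point concerns a stated choice. An SAP that adjusted would differ from the published text, which would then need aligning.

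A second defence is that the loss exists only relative to a better analysis. That stands. Unadjusted power rises slightly with R² and reaches the planned 80% throughout, so sizing and test agree.

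A third is that R² is unknown and may be small. That also stands. The common surgeon standard (at least 100 procedures and two reviewed videos) could narrow differences between sites. On the other side, the investigators chose these two factors as the ones to balance.

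Two stronger readings are tempting, and the document supports neither. A reader might infer that the analysis is invalid or that false positives are inflated. The error runs the other way: the test is conservative. A reader might also infer that the trial is underpowered, because two-sided power at 172 per arm is only about 70%. That figure comes from changing the sidedness, not from ignoring site and approach. The sample size section specifies a one-sided test and the analysis section gives no sidedness, so any such problem is a separate one.

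**Conclusion.** The point holds as one of efficiency. The stated analysis does not reflect the stated allocation, and where the factors are prognostic it overstates the standard error of the primary comparison. On the planned one-sided basis, adjustment gains nothing at R² = 0, about 1 point of power at 0.05, 2.3 points at 0.10 and 4.5 points at 0.20.

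These figures assume near-perfect balance on both factors, a total within-arm SD of 78.18 ml across the trial's sites, a true difference of 21 ml tested with no margin, and 172 evaluable patients per arm. They apply to a comparison of means. For the Mann–Whitney, categorical and log-rank tests the same conservative direction is expected, but its size was not calculated. The Cox model's covariates are unnamed, so it cannot be assumed either to include or to omit the two factors.

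**What to change.** In Data collection and analysis, replace the generic test for blood loss with, for example: the primary comparison is a linear model with treatment, site and the surgical approach recorded at randomisation; the treatment coefficient is reported with its confidence interval. State whether site is a fixed or random effect, and pool very small sites by a rule fixed before the analysts see allocation.

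The planning SDs are close to their means (66.4 against 72.5; 88.4 against 93.5) and differ between arms. Skewness and unequal variance should therefore be provided for in advance, by a transformation or robust standard errors, so that the Mann–Whitney option is not dropped without a replacement.

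For OS and DFS, stratify the log-rank test by approach, and use a Cox model stratified by approach with site as a stratum or random effect. Crossing site with approach gives up to 14 × 2 = 28 strata, averaging 382/28 ≈ 14 patients, which is a reason not to cross them in the log-rank test. Adjust the other secondary comparisons for the same two factors.

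Site and approach are already submitted to the data centre for allocation. The change needs no extra patients, visits or data, only protocol and SAP wording and minor analysis work.
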